### Study design

This is a 48-week, open-label, randomized, multicenter clinical trial conducted in three different university-affiliated hospitals in Seoul, Republic of Korea: Samsung Medical Center, Asan Medical Center, and Kyung Hee University Hospital. Subjects with T2DM will be randomly assigned to three groups in a 1:1:1 ratio. The control group “A” will receive routine diabetes care, with hospital visits every 3 months. Subjects in experimental group “B” will be introduced to the digital integrated healthcare platform to use at home without monitoring or assistance from medical staff. Subjects in experimental group “C” will be introduced to and educated on the healthcare platform for use and application at the hospital. Group C, unlike other groups, will also apply a CGMS for 1 week every 3 months. The medical staff will monitor the integrated healthcare data of group C subjects, including body weight, blood glucose, amount of exercise, and diet information, and will provide personal educational feedback via text message once a week. All subjects will visit a hospital at baseline and every 12 weeks thereafter for a total of 48 weeks (i.e., at week 12, 24, 36, and 48) and undergo a physical examination, blood and urine laboratory tests, and a Diabetes Treatment Satisfaction Questionnaire (DTSQ) at every visit. Figure 1 shows an overview of the study.

**Fig. 1 Fig1:**
[figure not shown]
Study design. The study group includes 3 groups: Control group A (no intervention and conventional diabetes management), Experimental group B (applying the digital integrated healthcare platform by themselves, no monitoring and feedback from medical staff), and Experimental group C (applying the digital integrated healthcare platform with monitoring and feedback from medical staff and applying a CGMS). This parallel study will be conducted for 48 weeks

### Digital integrated healthcare platform

The mobile healthcare platform “AutoChek Care” (Aprilis Co., Ltd.) is connected via Bluetooth to a glucometer, a scale with bioelectrical impedance analysis, a sphygmomanometer, and a watch-type pedometer. The collected health information from each device, including blood glucose level, body weight, body fat mass, blood pressure, number of steps, burned calories, and total walking distance, are automatically transmitted to the app. Because all the health information obtained by several devices as required for diabetes management is linked to one smartphone application, patients and clinicians can easily access the information and analyze the data.

### AI-based dietary management

The food recognition solution “FoodLens” (DoingLab Co., Ltd.) is an AI-based program that is able to recognize dozens of foods in a single photograph. Because it provides recognition of multiple food contents in a single photograph, patients do not need to take pictures of each food item individually. The program, which is based on deep learning technology of object detection and convolution neural networks, achieved a high recognition rate of 86.6% in food classification and the recognition rate was approved by “Korea Information Security Technology.” Data from this AI-based dietary program also are incorporated into the digital integrated healthcare platform.

### Continuous glucose monitoring system

Subjects in experimental group C will apply a CGMS (Dexcom G5^Ⓡ^) for 1 week every 3 months. The glucose concentration in the interstitial fluid is measured by a sensor attached to the skin and sent to the smartphone through a wireless transmitter using Bluetooth 4.0. The installed application, “Dexcom G5 Mobile App,” displays the measured values of glucose in the interstitial fluid on the screen every 5 min, provides changing patterns of glucose values, and alerts if the glucose level falls below or rises above the set values.

### Active monitoring and feedback by medical staff

For experimental group C, a medical staff member (a clinical dietitian from Amazing Food Solution Inc., Seoul, Korea) will introduce the platform to subjects, help them to configure the devices and app, and apply the platform to the patients at the hospital. They will motivate patients to maintain their self-care through ongoing personal monitoring and intervention. Educational intervention by text message regarding glucose level, weight control, dietary plan, and exercise plan will be conducted once a week.

### Participants

#### Eligibility criteria

The inclusion criteria are as follows: 1) aged ≥19 and < 70 years; 2) diagnosis of T2DM; 3) no prescription for any hypoglycemic agent within the previous 4 weeks or taking a consistent dose of one or more oral hypoglycemic agents for more than 12 weeks; 4) most recent measurements of hemoglobin A1c ≥ 53 and ≤ 69 mmol/mol within the previous 3 months; 5) body mass index (BMI) ≥ 23.0 kg/m^2^; 6) consent to utilize the digital integrated healthcare platform for diabetes care and research; and 7) voluntary signature of the informed consent form after being informed of the clinical trial. Exclusion criteria are as follows: 1) other types of DM including type 1 DM and gestational DM; 2) use of insulin or GLP-1 agonist injection; 3) history of uncontrolled chronic liver diseases such as hemochromatosis, hepatocellular carcinoma, autoimmune liver disease, liver cirrhosis, viral hepatitis (including hepatitis A, B, and C), or Wilson’s disease; 4) history of acute kidney injury (≥ 1.5 times increased serum creatinine); 5) history of psychological disorder such as schizophrenia, depression, or bipolar disorder; 6) use of anti-obesity medication; 7) history of alcoholism or drug addiction within the 3 months prior to screening; 8) use of drugs that affect glucose metabolism, such as corticosteroids and immunosuppressive drugs, within the 3 months prior to screening; 9) pregnancy, lactation, or planning for pregnancy; and 10) other problems that investigators consider to be inappropriate for participation in the trial.

### Recruitment

Subjects will be patients diagnosed with T2DM at one of three tertiary hospitals in Seoul, Republic of Korea: Samsung Medical Center, Asan Medical Center, and Kyung Hee University Hospital. Patients who voluntarily agree to participate in the clinical trial and who meet the inclusion criteria and none of the exclusion criteria will be enrolled. All participants will receive written information about the clinical trial and must provide written informed consent.

### Outcome variables

The primary outcome will be change in HbA1c from baseline to 6 months after intervention.

The main secondary outcome will be levels of HbA1c and fasting blood glucose at weeks 12, 24, 36, and 48. Other secondary outcomes include lipid profile (i.e., total cholesterol, high-density lipoprotein [HDL] cholesterol, triglycerides, and low-density lipoprotein [LDL] cholesterol) at weeks 24 and 48; the incidence of hypoglycemic events and adverse events at weeks 12, 24, 36, and 48; satisfaction evaluation according to the Diabetes Treatment Satisfaction Questionnaire (DTSQ) [9, 10] at weeks 12, 24, 36, and 48; mean body weight, BMI, and body fat mass for 1 week prior to weeks 12, 24, 36, and 48; mean number of steps, burned calories, and walking distance for 1 month prior to weeks 12, 24, 36, and 48; and mean calorie intake for 3 consecutive days prior to weeks 12, 24, 36, and 48. For experimental group C, secondary outcomes also include CGM metrics, specifically the values of mean glucose; coefficient of variation (CV); and percentages of time in range (TIR), time above range (TAR), and time below range (TBR) for 1 week prior to weeks 12, 24, 36, and 48, and the number of educational interventions by medical staff at weeks 12, 24, 36, and 48.

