## Background

Diabetes mellitus is one of the most common chronic diseases and incurs extensive social and economic costs. According to the International Diabetes Federation (IDF), there were approximately 463 million people (20–79 years) with diabetes globally in 2019, and the number is expected to rise to 700 million by 2045 [1]. It is widely known that not only medications, but also lifestyle managements such as diet, exercise, and weight control, are essential in the treatment of diabetes [2–4]. Recently, advances in mobile technology have led to a large number of smartphone applications (apps) that aim to facilitate self-management of diabetes mellitus (DM) [5–8].

Although numerous healthcare apps have been developed for patients with diabetes, few of them are consistently used due to limitations. First, it is inconvenient to input multiple dietary data points. Dietary control is important in diabetes management, so feedback based on the dietary record is required. However, patients often struggle to record their dietary information reliably because it is difficult to search and enter every food item eaten into the smartphone healthcare apps. In addition, it is hard to convert the various entered foods into actual dietary data such as nutritional composition and calories. Moreover, because values of blood glucose measured by a home glucometer have to be manually entered into the apps, there are multiple opportunities for typographical errors in the glucose records. Recently, Bluetooth technology has allowed for values of blood glucose by a glucometer to be automatically recorded in any linked smartphone apps. However, due to the discomfort of the finger-prick blood test, patients do not often measure their blood glucose level. Also, most diabetes self-management apps require users to assess their body weight, blood pressure, and amount of exercise using a scale, sphygmomanometer, and pedometer, respectively, and then manually input those values. Although some healthcare apps can now be linked to devices via Bluetooth so that health information is automatically recorded into the apps, various biometric data such as blood glucose level, body weight, blood pressure, and amount of exercise are not integrated and must be provided separately for management of diabetes. In addition, most patients are inconsistent in use of these apps on their own without feedback from medical staff.

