### Anthropometric and vital sign measurements

At each clinical visit, vital signs including blood pressure, heart rate, and, body weight, and BMI will be collected.

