### Distribution and use of at-home measurement devices and the digital integrated healthcare platform

For subjects in experimental groups B and C, at-home measurement devices of a Bluetooth-enabled glucometer, scale with bioelectrical impedance analysis, sphygmomanometer, and watch-type pedometer will be provided. Subjects in group B will configure and apply these devices and the platform by themselves, while subjects in group C will be provided instruction regarding the configuration and use of the devices and the platform by medical staff during their hospital visit.

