## Discussion

In this study, the effect of a digital integrated healthcare platform will be investigated in patients with type 2 diabetes who have HbA1c 53–69 mmol/mol (7.0–8.5%) and body mass index (BMI) ≥ 23 mg/m^2^. We plan to apply a digital integrated healthcare platform using an artificial intelligence (AI)-based dietary management solution and a continuous glucose monitoring system (CGMS), and medical staff will continuously monitor the collected healthcare data and send regular educational messages via the platform to encourage efficient self-management of diabetes.

Previously, the efficacy of several smartphone apps for diabetes management was demonstrated via randomized controlled trial [5, 6]. However, even if the efficacy of apps has been demonstrated in clinical trials, the effect may decrease if the patient does not actively use the apps. In 2016, Payal Agarwal et al. [12] investigated the impact of “Bluestar,” an application developed for self-management of diabetes and approved by the Food and Drug Administration, among different clinical sites and health systems. They conducted a pragmatic, multicenter, randomized trial in three recruitment sites. They reported low usage of the app among participants, with a mean number of log-in days of 42.4 (SD 52.1) over 26 weeks, with 46.4% (51/110) of the participants using the app for 10 days or less, and the results showed no difference in HbA1c between the intervention and control groups [12].

One of the strengths of the present study is the use of an AI-driven dietary solution for the record of dietary intake. The image-assisted dietary assessment was shown in previous studies to reduce underreporting of dietary intake compared with traditional methods [13]. The dietary program in this study is expected to be more convenient and effective in that it recognizes all foods by a single capture utilizing the AI solution. Also, for user-friendliness, participants can see their various healthcare data, such as glucose level, body weight, blood pressure, daily activity, and dietary data, on the digital integrated healthcare platform app by connecting Bluetooth-enabled at-home measurement devices including a glucometer, scale, sphygmomanometer, and watch-type pedometer.

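### Body weight and BMI are defined as home-scale means that group A cannot have, although clinic values exist in every arm; the other device outcomes depend on platform use that is supported in C but not in B

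*Protocol article*

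**What the plan says.** Outcome variables in the protocol article lists three sets of secondary outcomes as averages over a window before each visit. The weight-related set reads "mean body weight, BMI, and body fat mass for 1 week prior to weeks 12, 24, 36, and 48". Activity is averaged over a longer window, and that entry reads "mean number of steps, burned calories, and walking distance for 1 month prior to weeks 12, 24, 36, and 48". Calorie intake is averaged over three days in a row ahead of the same visits.

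The equipment is limited to two arms: "For subjects in experimental groups B and C, at-home measurement devices of a Bluetooth-enabled glucometer, scale with bioelectrical impedance analysis", together with a sphygmomanometer and pedometer. The Dietary data section likewise takes dietary information from the app in B and C only.

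Support differs between these two arms. "Subjects in group B will configure and apply these devices and the platform by themselves", whereas C is instructed by staff at the hospital. Under Intervention, B has no monitoring or intervention. C gets weekly messages and, in four 3-day periods at 12-week intervals, encouragement to keep dietary records with a message each day.

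Separately, and without restriction to any arm: "At each clinical visit, vital signs including blood pressure, heart rate, and, body weight, and BMI will be collected".

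The secondary hypothesis includes body weight, body fat mass, amount of exercise and dietary information among the parameters expected to improve in platform users relative to routine care.

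**The concern.** A window mean exists only if something was recorded in the window. For weight and BMI the definition relies on a home scale that group A does not have, so the outcome as written cannot serve the comparison with routine care that the hypothesis states. It also leaves unscored any B or C patient who attends the visit but did not use the scale that week.

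For fat mass, activity and calorie intake there is no substitute measurement. Whether a patient has a value depends on use of the intervention's own tools, and C is helped and prompted to use them while B is not. The Background itself expects that "most patients are inconsistent in use of these apps on their own without feedback from medical staff". If the patients who record differ between B and C in ways related to outcome, a comparison of recorders is no longer a comparison of the randomised groups.

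**Working it through.** **Step 1. Source of each outcome, by arm.**

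| Outcome | Window | Described source | A | B and C |
|---|---|---|---|---|
| Weight, BMI as defined | 1 week before visit | home scale | no value | only if weighed that week |
| Weight, BMI at clinic | the visit | clinic measurement | yes | yes |
| Body fat mass | 1 week | home scale (bioimpedance) | no value | only if scale used |
| Steps, burned calories, distance | 1 month | watch-type pedometer | no value | only if worn |
| Calorie intake | 3 days | meal photograph in app | no value | only if meals recorded |

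The article does not state outright that the 1-week weight mean comes from the home scale. It describes no other source that could give several readings in the week before a visit.

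Table 1 also schedules vital signs at baseline, and the platform is first applied at that visit. The clinic series therefore has a baseline value, whereas a home mean for the week before baseline would not exist.

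**Step 2. How many patients the weight definition leaves out.** From Sample size assumptions: 78 / (1 − 0.20) = 97.5, rounded up to 98 per group; 3 × 98 = 294. This reproduces the article's 98 and 294, which are set for HbA1c; no figure is given for the device outcomes. Group A is 98 / 294 = 33.3% of those randomised. At most 196 patients can have the outcome as defined, before any non-use in B or C. With clinic values, every patient who attends has one.

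**Step 3. The remaining device outcomes.** With no source in A, the only randomised comparison open to them is B versus C. Even B's data are described inconsistently: the section on data acquisition by the platform names group C only, while Table 1 lists platform data collection for B and C.

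**Step 4. Illustration of what selection could do.** All inputs are assumptions. Suppose a patient is recorded when a latent engagement score exceeds a threshold, and that score has correlation ρ with the outcome (higher = better). With a true C minus B difference of zero, a recorders-only comparison has

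bias = ρ × [m(p_C) − m(p_B)], where m(p) = φ(z_{1−p}) / p,

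p is the share recorded, and φ is the standard normal density.

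- m(0.536) = 0.741, m(0.80) = 0.350, m(0.90) = 0.195, m(0.95) = 0.109. Here 0.536 = 1 − 51/110, the complement of the low-use share in the cited trial.
- p_B = 0.536, p_C = 0.80, ρ = 0.3: 0.3 × (0.350 − 0.741) = −0.12 SD. With ρ = 0.5: −0.20 SD. The SE is √(1/52.6 + 1/78.4) = 0.178 SD.
- p_B = 0.536, p_C = 0.90, ρ = 0.3: −0.16 SD; a nominal 5% test would reject about 16% of the time.
- p_B = 0.536, p_C = 0.95, ρ = 0.5: −0.32 SD; rejection about 45%.
- p_B = p_C, or ρ = 0: bias 0, rejection 5%.

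Over p_B from 53.6% to 80%, p_C from 80% to 95% and ρ from 0 to 0.5, the bias runs from 0 to −0.32 SD. This shows only that the mechanism could matter; it is not an estimate for this trial.

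**The case against.** The strongest reply is that the article gives no rule for an empty window, no minimum number of recording days and no missing-data method, and that an article may leave these to the full protocol or SAP. That stands: their absence is not the point here. It does not cover weight and BMI, where the stated definition itself excludes a randomised arm.

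Second, no B versus C test is named; the secondary hypothesis compares platform users with routine care. That also stands, and it limits the second half of the point to what could follow if B and C are compared. For body weight it works the other way, since the comparison that is hypothesised is the one the definition cannot supply.

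Third, clinic weight and BMI are collected anyway, so no data are lost and the choice of reading is a preference. The first part is right and makes the remedy cheap. The second is not: the article does not say that clinic values stand in for A, and if they did, a single clinic reading in A would be set against a home mean in B and C.

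A reader might go further and infer that non-recorders are dropped, that nearly half of B will be missing, and that B is therefore flattered by a known amount. The documents do not support this. They do not say that such patients are dropped. The cited figure, "with 46.4% (51/110) of the participants using the app for 10 days or less", is low use of a different app over 26 weeks, not an empty window here; a patient with a few records still yields a mean, and inconsistent use is not absence of use. Automatic Bluetooth transfer may also ease recording. The direction is open as well: calorie intake depends on amounts that the patient enters, so fuller recording under daily prompting in C could raise its measured intake.

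**Conclusion.** The point holds in two parts of unequal strength.

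For body weight and BMI it rests on the article's own text, with the single inference that a 1-week mean needs the home scale. As defined, the outcome has no value in one third of randomised patients and cannot address the stated comparison with routine care, while usable values are collected in all arms.

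For body fat mass, steps, burned calories, distance and calorie intake the point is a risk, not a demonstrated bias. It requires both that recording differs between B and C, which the unequal support makes plausible, and that recording is related to outcome. The recording rates, the correlations and the 0 to 0.32 SD range are assumptions, and neither size nor sign can be derived from the documents. These are all secondary outcomes; the primary HbA1c outcome comes from visit laboratory tests and is unaffected.

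**What to change.** 1. In Outcome variables, define body weight and BMI as the values measured at the clinic visit in all three arms. Keep the 1-week home mean in B and C as a supportive measure.
2. For body fat mass, steps, burned calories, distance and calorie intake, report by arm the share of randomised B and C patients who have a scorable window at each visit, and label B versus C means among recorders as descriptive. Any minimum-recording rule or sensitivity analysis for non-recorders can sit in the SAP.
3. Reconcile the data-acquisition section with Table 1 on whether platform data are collected in B.

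The cost is wording and a simple tabulation; no new data are needed. The downside is that a single clinic weight is somewhat noisier than a 1-week mean, and that the device-based results carry a weaker claim.

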### Sample size assumptions

Assuming a 0.3% difference in HbA1c values between the study groups (mean HbA1c 58 mmol/mol (7.44%) [standard deviation, 0.6%]) (effect size d = 0.50) according to previous studies, [7, 11] 78 subjects per group are required, with a two-sided alpha threshold of 0.05 and 80% power. Considering a dropout rate of 20%, the total number of patients required for this study is estimated to be 294 (98 patients per group) from the collective three hospitals.

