### Data analysis

Baseline comparisons between groups for continuous variables will be performed using the two-sample t-test for normally distributed outcomes or Wilcoxon’s rank-sum test for non-normally distributed outcomes. Pearson’s chi-square or Fisher’s exact test will be used for categorical variables. Changes from baseline in each group will be compared by McNemar’s test for proportions and the paired t-test or Wilcoxon signed-rank test for means.

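### The sample size rests on the SD of HbA1c levels while the primary outcome is a change, and no baseline-adjusted analysis is stated to link the two

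*Protocol article*

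**What the plan says.** Protocol article, Sample size assumptions: the planning difference is one of values, and the SD is attached to a mean level: "Assuming a 0.3% difference in HbA1c values between the study groups (mean HbA1c 58 mmol/mol (7.44%) [standard deviation, 0.6" percent. Their ratio is the stated "effect size d = 0.50". The error rates are given as "with a two-sided alpha threshold of 0.05 and 80% power", and the result is that "78 subjects per group are required". Allowing for 20% dropout, this becomes 98 per group and 294 in total.

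Outcome variables: "The primary outcome will be change in HbA1c from baseline to 6 months after intervention". HbA1c levels at weeks 12, 24, 36 and 48 appear separately, under the main secondary outcome.

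Data analysis: two-sample tests are named for comparing groups at baseline. For change the section says "Changes from baseline in each group will be compared by" McNemar's test, the paired t-test or the signed-rank test, which are within-group tests. It names no between-group analysis of the primary outcome and no adjustment for baseline HbA1c.

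**The concern.** A level and a change from baseline generally have different SDs. With equal SDs at the two times, the SD of the change equals the SD of the level only when the baseline-to-follow-up correlation is exactly 0.5. A lower correlation makes the change more variable and a higher one makes it less so. The article treats level and change as separate outcomes, powers the trial with the SD of one and takes the other as primary, and gives neither a correlation nor an SD of change.

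The stated 80% power therefore does not follow for the primary outcome until the between-group analysis is known. If that analysis were a plain comparison of changes and the correlation were low, the trial could miss the 0.3% difference more often than planned. If it adjusts for baseline, the SD of the level is a cautious input.

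**Working it through.** **Inputs.** From Sample size assumptions: difference 0.3%, SD 0.6%, two-sided alpha 0.05, 78 evaluable per group, dropout 20%. Not in the document and therefore assumed: the correlation r between baseline and week-24 HbA1c (0 to 0.7 shown) and, except in step 4, SD 0.6% at both times. Power is from the two-sample t-test.

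**1. The plan's own figures.**
- d = 0.3/0.6 = 0.50, as stated.
- A two-sample t-test with d = 0.50, two-sided alpha 0.05 and 80% power needs 63.8, so 64 per group. With 78 per group its power is 87%.
- The figure of 78 is reproduced by alpha 0.025 per comparison (77.3, so 78). It is also matched by a three-group ANOVA at 0.05 with equally spaced means (78.1). The document states neither basis. Both use the SD of 0.6%.
- Dropout: 78/0.8 = 97.5, so 98 per group, and 3 × 98 = 294. This agrees.

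**2. Change compared between groups without adjustment.** SD of change = 0.6 × √(2(1 − r)).

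| r | SD of change (%) | d | Power, 78 per group, alpha 0.05 |
|---|---|---|---|
| 0 | 0.849 | 0.354 | 59% |
| 0.3 | 0.710 | 0.423 | 75% |
| 0.4 | 0.657 | 0.456 | 81% |
| 0.5 | 0.600 | 0.500 | 87% |
| 0.7 | 0.465 | 0.645 | 98% |

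Power reaches 80% at r of about 0.39 (SD of change about 0.66). If alpha 0.025 per comparison was intended, the break-even is r = 0.50.

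**3. ANCOVA adjusted for baseline.** Residual SD = (week-24 SD) × √(1 − r²), here 0.6 × √(1 − r²).

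| r | Residual SD (%) | Power, 78 per group, alpha 0.05 |
|---|---|---|
| 0 | 0.600 | 87% |
| 0.3 | 0.572 | 90% |
| 0.5 | 0.520 | 95% |
| 0.7 | 0.428 | 99% |

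The residual SD never exceeds the week-24 SD. So if the week-24 SD is at most 0.6%, power is at least 87% for any r from 0 up (at least 80% at alpha 0.025).

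**4. Effect of the entry range.** Eligibility limits HbA1c to 53–69 mmol/mol (7.0–8.5%). If entry values were spread evenly over that range (an assumption), the baseline SD would be 1.5/√12 = 0.43%. With week-24 SD 0.6% and r = 0.3, the SD of change is √(0.43² + 0.6² − 2 × 0.3 × 0.43 × 0.6) = √0.390 = 0.625%. Power is then 85% at alpha 0.05, compared with 75% under equal SDs. The break-even r falls to about 0.20.

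**The case against.** The strongest reply is that the document does not plan an unadjusted comparison. It names no between-group test of the primary outcome at all, and a journal article may leave the model to the full protocol or analysis plan. Under a baseline-adjusted model, sizing on the SD of levels is cautious. This stands: a reader might infer from the paired tests that raw changes will be compared between groups, but the text does not say so.

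A reader might also infer that the trial is under-powered. The document does not support that either. Nothing in it puts r below 0.39, and at the stated alpha 78 per group is more than the 64 that the stated inputs require. The stricter break-even of 0.50 needs an alpha of 0.025, which is not stated and is not the only route to 78.

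Nor does the narrow entry range clearly worsen matters. It may lower r, but it also lowers the baseline SD, and step 4 shows that the second effect can offset much of the shortfall.

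What survives is narrower. The planning SD and the primary outcome refer to different quantities, and the article does not state the analysis that would make the one a safe input for the other. A fuller document could supply the model, but the sample size section would still need to say how its SD relates to the outcome.

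**Conclusion.** The mismatch is real, and its consequence is conditional. For a between-group comparison of change without adjustment, with 78 per group, a true difference of 0.3%, SD 0.6% at both times and alpha 0.05, power ranges from 75% at r = 0.3 to 98% at r = 0.7. It falls short of 80% only below r of about 0.39, and a smaller baseline SD moves that point lower.

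With baseline adjustment the shortfall disappears, provided the week-24 SD is no more than 0.6%. That condition cannot be checked here, because the studies cited for the planning figures are not available. This is a worthwhile clarification that improves the analysis at no cost in patients. It gives no reason to enlarge the trial.

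**What to change.** In Data analysis, name the primary analysis: ANCOVA of week-24 HbA1c (or of the change) on treatment group, adjusted for baseline HbA1c, with contrasts B versus A and C versus A. In Sample size assumptions, say that 0.6% is the SD of the level, and that it is a conservative bound on the ANCOVA residual SD provided the week-24 SD does not exceed 0.6%. Keep 98 per group.

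The cost is wording in two sections. Laboratory tests already schedules HbA1c at baseline and week 24, so no extra measurement or patient is needed.

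### The stated 78 per group does not follow from the stated inputs: d = 0.50 at two-sided alpha 0.05 and 80% power needs 64, so the basis of the calculation must be confirmed and restated

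*Protocol article*

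**What the plan says.** All the inputs stand in one paragraph of the protocol article, under Sample size assumptions:

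- Difference: "Assuming a 0.3% difference in HbA1c values between the study groups".
- Spread: "standard deviation, 0.6"%, and from these "effect size d = 0.50".
- Result and error rates: "78 subjects per group are required, with a two-sided alpha threshold of 0.05 and 80% power".
- Attrition: "Considering a dropout rate of 20"%, which raises the figure to 98 per group and 294 in total.

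Under Study design, the allocation is given as: "Subjects with T2DM will be randomly assigned to three groups in a 1:1:1 ratio". The Hypotheses section sets platform users, with or without staff feedback, against routine care; with the three-group design this points to two comparisons, B vs A and C vs A. The sample size paragraph mentions no divided alpha, no adjustment for several comparisons and no three-group test. The Data analysis section names two-sample tests for baseline comparisons and paired tests for within-group change. It sets no alpha for the primary between-group comparison.

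**The concern.** A standardised difference d, a two-sided alpha and a power are the inputs of a two-group comparison of means, and together they fix the sample size. Here they fix it at 64, and the article prints 78. The excess is too large for rounding, and the dropout allowance is applied afterwards as a separate step.

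What is at stake is the significance threshold for the primary endpoint, not the number recruited. If 78 came from 0.025 per comparison, the planned size already pays for family-wise control at 0.05, but the published sentence shows only 0.05. An analyst who took that as the level for each comparison would use a looser threshold than the design assumed. With two comparisons sharing one control arm of equal size, testing each at 0.05 gives a family-wise error of about 9% when neither platform arm has an effect (normal approximation, correlation 0.5 between the two test statistics).

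**Working it through.** **Inputs** (Sample size assumptions): difference 0.3, SD 0.6, two-sided alpha 0.05, power 0.80, dropout 20%. Effect size: d = 0.3/0.6 = 0.50, which agrees with the article.

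**1. The article's figure from its own inputs.** Normal approximation: n per group = 2(z₁₋α/₂ + z_power)²/d² = 2(1.960 + 0.842)²/0.25 = 62.8, so 63. The exact two-sample t-test (noncentral t) gives 63.77, so 64. The stated 78 is not reproduced; it is 14 more than 64 (14/64 = 22%).

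**2. Dropout step.** 78/(1 − 0.20) = 97.5, so 98 per group, and 3 × 98 = 294. This reproduces, so the discrepancy lies wholly in the 78. For comparison, 64/0.80 = 80 per group, and 3 × 80 = 240.

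**3. Power that 78 per group gives** (t-test, d = 0.50):

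| Two-sided alpha | n needed for 80% power | Power at 78 |
|---|---|---|
| 0.05 | 63.77, so 64 | 87.3% |
| 0.025 (0.05/2) | 77.31, so 78 | 80.4% |
| 0.0167 (0.05/3) | 85.20, so 86 | 75.8% |

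At alpha 0.05, 80% power with 78 per group corresponds to d of about 0.45, not 0.50.

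**4. Other routes to 78.**

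- One-sided alpha 0.05: 50 to 51. Does not reach 78.
- Rank-sum test, inflating the t-test size: 63.77/0.955 = 66.8, about 67; in the worst case 63.77/0.864 = 73.8, so 74. Does not reach 78.
- Three-group F test at 0.05 with means 0, 0.15 and 0.30 and SD 0.6: 78.08, so 79; power at 78 is 79.95%. This comes within one subject, but needs a middle mean that the article does not state.
- The same F test with means 0, 0 and 0.30: 59. Does not reach 78.
- Dunnett's test for two comparisons with control, family-wise 0.05: 76. Close, but it is also an adjustment that the article does not mention.

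The only route tried that is two-sided, uses d = 0.50 and 80% power, and gives exactly 78 is the t-test at alpha 0.025.

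**The case against.** The strongest reply is that nothing is miscalculated. The article gives a threshold of 0.05 without saying that it applies to each comparison. If 0.05 is the family-wise level, halved over B vs A and C vs A, then 0.05, 80% and 78 are all true together and the only defect is an unstated split. This stands in part. A reader might infer that the stated alpha, power and sample size are irreconcilable; the document does not support going that far. It supports the narrower statement that they do not agree for a single two-group comparison at 0.05, which is the plain reading of a paragraph that mentions no division.

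A reader might also infer that the design certainly rested on 0.025 and that multiplicity control has since been lost. That is not established either. A three-group F test with the middle mean halfway has 79.95% power at 78, which rounds to the stated 80%. It fits a two-sided threshold and an effect size d poorly, and it needs an unstated mean, so 0.025 remains likelier, but as an inference.

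Detailed multiplicity rules may sit in the full protocol or analysis plan, which are not shown, and their absence from an article is no fault. That does not cover a printed sample size that its own printed inputs fail to reproduce.

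Finally, the discrepancy is in the safe direction for power. This is correct, and it limits the point to clarification. The contrast of 294 with 240 is no argument for recruiting fewer patients.

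**Conclusion.** The sentence is wrong as written. For a two-group comparison at two-sided alpha 0.05 with d = 0.50 and 80% power, the requirement is 64 per group (63 by normal approximation), against 78 stated; 78 gives about 87% power. These figures assume equal group sizes, a common SD of 0.6% and a t-test at the stated level for each comparison. The likeliest explanation is an unreported 0.025 per comparison, at which 78 per group gives 80.4% power, but the document does not confirm it. The trial is not underpowered at the stated alpha, and the totals of 98 and 294 follow correctly from 78. The live risk is a mismatch between the alpha used in the primary test and the alpha on which the design was built.

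**What to change.** Confirm from the original calculation how 78 was obtained, then restate the sentence before outcome data are seen, in whichever of these forms is true:

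1. 78 per group give 80% power for each of two comparisons with control (B vs A and C vs A) at two-sided alpha 0.025 each, family-wise 0.05. The primary analysis must then use 0.025 per comparison.
2. 78 per group give about 87% power per comparison at two-sided alpha 0.05.
3. The calculation rests on an omnibus three-group test or another multiple-comparison procedure. In that case name it and give the means assumed for all three groups. If it is the F test with a midway mean, the exact requirement is 79 and power at 78 is 79.95%.

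The cost is one sentence, plus a matching statement of the alpha in the primary analysis. Enrolment stays at 98 per group, 294 in total.
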